## Abstract

**Introduction:**

Chronic respiratory diseases (CRDs), such as asthma and chronic obstructive pulmonary disease (COPD), are among the leading non-communicable diseases (NCDs) worldwide. However, diagnosing CRDs in low-income and middle-income countries (LMICs) remains challenging due to limited access to spirometry and trained professionals. Aggravating the burden, CRDs often coexist with other NCDs, increasing healthcare costs, reducing quality of life and elevating mortality. These challenges highlight the need for simple case-finding approaches for CRDs, such as the COPD in Low-Income and Middle-Income Countries Assessment (COLA-6) questionnaire, to support prompt identification and appropriate care within NCD services in LMICs.

**Objective:**

To evaluate the discriminative accuracy, feasibility and implementation of the COLA-6 questionnaire in identifying and managing CRDs in Brazilian Primary Healthcare (PHC) services for NCDs.

**Methods and analysis:**

The Multimorbidity Approach for REspiratory Solutions (MARES) study consists of three work packages to be conducted in PHC services in São Carlos/SP and São Paulo/SP, Brazil.

MARES-1: A cross-sectional observational study enrolling 859 individuals with at least one NCD receiving care in PHC. The COLA-6 questionnaire will be administered by the research team and compared with quality-assured spirometry. The Chronic Airways Assessment Test (CAAT), Asthma Control Questionnaire (ACQ-7) and fractional exhaled nitric oxide (FeNO) will also be assessed. The diagnostic performance of COLA-6 for identifying CRDs—including COPD, asthma, preserved ratio impaired spirometry, restriction and overlaps—will be assessed using area under receiver operating characteristic curves and 95% CIs.

MARES-2: A cross-sectional observational study enrolling 20 healthcare professionals (physicians, physiotherapists, community health agents and nurses) from five PHC services. These professionals will apply the COLA-6 during routine NCD care to a total sample of 1000 patients. Qualitative interviews will be conducted to explore barriers and facilitators to the implementation of COLA-6, using deductive thematic analysis.

MARES-3: A longitudinal, prospective observational study in which patients from MARES-1 and MARES-2 will be reassessed at 6-month follow-up. A total sample of 473 participants with abnormal spirometry, a diagnosis of CRD or high risk for CRDs is expected. Participants will undergo spirometry, and a subset will be interviewed to explore their healthcare experiences through qualitative thematic analysis. Access to diagnostic and treatment services in Brazil will be assessed. Changes in spirometry values, FeNO, CAAT and ACQ-7 scores from baseline to 6 months in patients from MARES-1 will be analysed.

**Ethics and dissemination:**

This study has been approved by the Ethics Committees of Federal University of São Carlos and University of Santo Amaro (UNISA). Ethical approval was also granted by the University College London. Results will be disseminated through peer-reviewed medical journals and presentations at international conferences. Results will improve identification of CRDs, addressing a significant gap in current PHC settings.

**Trial registration number:**

NCT07050823/NCT07093021/NCT07134855.

STRENGTHS AND LIMITATIONS OF THIS STUDYConsiders chronic respiratory disease (CRD) diagnoses including asthma and chronic obstructive pulmonary (COPD) disease together and in the setting of established care for non-communicable diseases.Assesses the real-world feasibility of implementing the COPD in Low-Income and Middle-Income Countries Assessment questionnaire (COLA-6) among healthcare professionals and patients in primary healthcare (PHC) settings.Multiphase, mixed-methods approach combining cross-sectional and longitudinal designs with both quantitative and qualitative analyses.Findings may be specific to Brazil’s PHC system and may not be directly generalisable to other healthcare settings or regions in low-income and middle-income countries.A 6-month follow-up may not fully capture long-term outcomes related to improved CRD diagnosis and management.

## Introduction

 Chronic respiratory diseases (CRDs) are among the most prevalent chronic non-communicable diseases (NCDs) worldwide.^1^ Asthma and chronic obstructive pulmonary disease (COPD) are the most common CRDs.^2^ The global prevalence of asthma was 262 million people in 2019, causing 455 000 deaths, while COPD was responsible for 480 million cases in 2020 and approximately 3 million deaths in 2019.^2^,^5^ High-income countries report higher COPD prevalence than low-income and middle-income countries (LMICs), partly due to age distribution differences and underdiagnosis. However, rising life expectancy in LMICs may lead to an increased prevalence.^6^ The combined prevalence of asthma and COPD exceeds that of diabetes (463 million) or HIV infection (39 million).^7 8^

To confirm COPD and asthma in individuals presenting with characteristic symptoms, lung function must be evaluated, most often through spirometry, a test that remains scarce in LMICs, including Brazil, where the majority of people with CRDs live.^9^,^14^ Spirometry requires specific equipment, resources for implementation within health systems, trained professionals to perform the exam and clinicians capable of interpreting the results.^12^ Consequently, many patients with CRDs are either not diagnosed or are diagnosed late in the course of the disease. Undiagnosed and consequently untreated patients make significant use of healthcare services and are at increased risk of disability, acute exacerbations and premature death.^15^ When diagnosed early, with greater treatment potential, a lower disease burden and a better long-term prognosis become possible.^16^ This aligns with the recent resolution of the 78th World Health Assembly, which calls for strengthening primary healthcare (PHC) through integrated strategies, recognising shared risk factors among lung and other NCDs, and promoting evidence-based, cost-effective approaches for early detection and treatment.^17^

Prompt identification of CRDs is therefore crucial not only for those affected but also for the health system and society as a whole. Given the previously described barriers to CRD diagnosis, alternative approaches to conventional spirometry for detecting undiagnosed and untreated cases are required to enable earlier therapeutic management, reduce symptoms, and the frequency and severity of respiratory infections (exacerbations), and ultimately improve quality of life and survival.^18^

As a strategy for identifying individuals at risk of CRDs in LMICs, particularly COPD, Siddharthan *et al*^19^ developed and validated a simple ‘case-finding’ tool comprising a seven-item questionnaire combined with a simple measurement of lung function (peak expiratory flow or PEF): the ‘COPD in Low-Income and Middle-Income Countries Assessment’ (COLA). The ‘Global Excellence in COPD Outcomes’ (GECo) group demonstrated the discriminative accuracy of the tool in identifying individuals with COPD in a sample of 10 664 people from three LMICs (Nepal, Peru and Uganda). In that study, COLA was applied in a short version (COLA-6) and found to be feasible and accurate.^19^ However, the authors emphasised the need to test the performance of COLA-6 in other LMICs and to determine whether its implementation by clinicians rather than research staff is associated with improved clinical outcomes. The COLA-6 questionnaire has since been translated and cross-culturally adapted into Brazilian Portuguese for use in Brazil.^20^ In general, previous studies have considered asthma and COPD separately, yet in a PHC setting, it may be more cost-effective to consider CRDs together. Indeed, there is a third, prevalent pattern of spirometric abnormality termed PRISm (preserved ratio impaired spirometry) that is also associated with significant respiratory morbidity and mortality.^21^

In parallel with the burden of CRDs, there has been growing interest in and concern about multimorbidity, defined as the coexistence of at least two long-term conditions in the same individual.^22 23^ CRDs frequently coexist with other NCDs, and this coexistence has been associated with increased hospital admissions and healthcare costs, as well as reduced quality of life and exercise tolerance.^24^ Furthermore, the risk of comorbidities is higher in patients with COPD compared with matched controls, and these comorbidities strongly influence mortality.^25^ Case-finding for undiagnosed COPD in people with hypertension appears feasible in PHC in Brazil,^26^ but the benefit to individuals and society remains to be defined. Multimorbidity in patients with asthma can contribute to an increase in symptoms and worsening control of the disease.^27^ Although the mechanisms underlying the relationship between CRDs and other chronic diseases are not yet fully understood, several have been proposed, including shared environmental exposures (eg, tobacco use, air pollution, biomass smoke), physical inactivity (driven by dynamic hyperinflation, muscle wasting) and accelerated ageing (cellular senescence, systemic inflammation, oxidative stress).^24^

In summary, a more comprehensive approach to individuals with CRDs—considered collectively—and multimorbidity is essential for the development of multidimensional assessment and holistic care strategies aimed at improving patient outcomes^28^ and reducing health service burden. Thus, considering the complexity of these patients, and through the lens of multimorbidity, there is a strong clinical and public health rationale for identifying people living with undiagnosed CRDs during routine care for other NCDs in PHC services. This would be of particular value in LMICs, including Brazil. However, despite its potential benefits, it remains unknown whether case-finding approaches using simple tools like COLA-6 can be effectively implemented during routine NCD care and what the short-term and longer-term benefits may be for both patients and the broader healthcare system.

### Objective

*Multimorbidity Approach for*
*REspiratory Solutions (MARES-1)*: To evaluate the discriminative accuracy of the COLA-6 questionnaire in identifying Brazilian individuals with CRDs who attend PHC services for the management of other NCDs.

*MARES-2*: To assess the feasibility of implementing the COLA-6 questionnaire in PHC settings for NCD care in Brazil by the PHC professionals.

*MARES-3*: To investigate how individuals with NCDs attending PHC services, identified as having abnormal spirometry, CRD or high risk for CRDs, access further diagnostic and treatment services in Brazil.

## Methods and analysis

### Study design overview

This study is delivered as an equitable international partnership between University College London (UCL), UK, and the Federal University of São Carlos (UFSCar), Brazil. The project spans 4 years, beginning in 2025 and planned to conclude in 2028, and it is entitled MARES—Multimorbidity Approach for REspiratory Solutions. Ethical approval has been granted by the Human Research Ethics Committee of UFSCar and National Research Ethics Commission and the University of Santo Amaro (UNISA) (reference number: MARES-1: 85805425.4.1001.5504; MARES-2: 85837225.7.1001.5504; MARES-3: 85813325.3.1001.5504), a collaborating partner institution of the Basic Health Unit (BHU) in São Paulo/SP. Ethical approval was also granted by UCL Research Ethics (reference: 2024/0048). All participants will have their identities and personal data treated with strict confidentiality. Participation will only take place after signing the Informed Consent Form, corresponding to the specific study in which they are enrolled. The studies have been registered at clinicaltrials.gov as MARES-1 (NCT07050823), MARES-2 (NCT07093021) and MARES-3 (NCT07134855).

*MARES-1*: This study aims to evaluate the discriminative capacity of the COLA-6 questionnaire in identifying individuals with CRDs who attend PHC services in Brazil for the treatment of other NCDs. To achieve this, we will conduct a cross-sectional observational study enrolling 859 individuals with one or more existing NCDs who are receiving care in PHC services. The COLA-6 questionnaire will be administered, and its results will be compared with gold-standard postbronchodilator spirometry. The performance of the case-finding tool will be assessed using the area under a receiver operating characteristic (ROC) curve for CRDs considered collectively and separately.

*MARES-2*: This study aims to evaluate whether the COLA-6 questionnaire is feasible to be implemented by health professionals during routine NCD care in PHC services in Brazil. For this purpose, we will conduct a cross-sectional observational study enrolling 20 healthcare professionals (physicians, physiotherapists, community health agents and nurses) from five PHC services to apply the COLA-6 questionnaire during routine NCD care. This is expected to result in a total sample of 1000 patients. Qualitative interviews will be conducted with the healthcare professionals to explore barriers and facilitators to implementing the COLA-6 in clinical practice.

*MARES-3*: This study aims to investigate how individuals attending PHC services in Brazil for NCD treatment, who are either identified as having abnormal spirometry or a diagnosis of CRD in MARES-1 or identified as being at high risk for CRDs through the COLA-6 questionnaire in MARES-2, access further diagnostic and treatment services. To this end, we will conduct a longitudinal, prospective observational study. This follow-up study, at 6 months, will include an estimated sample of 309 individuals with abnormal spirometry results or diagnosis of CRDs from MARES-1 and an estimated sample of 164 individuals identified as being at high risk for CRDs through the COLA-6 questionnaire in MARES-2, resulting in an estimated total sample of 473 participants. Qualitative interviews will be conducted with a diverse subsample of 30 participants, to explore the barriers and facilitators to accessing the healthcare system for diagnosis and treatment, while all participants will undergo basic data collection during follow-up.

### Study setting

This study will be conducted in PHC services, including BHUs and Family Health Units (FHUs), located in the municipalities of São Carlos and São Paulo, both situated in the state of São Paulo, Brazil. The municipality of São Carlos has a population of 254 857 inhabitants and a gross domestic product (GDP) of R$55 044.88 per capita,^29^ with 34 PHC units.^30^ In contrast, São Paulo, the state capital, has a population of 11 451 999 inhabitants and a per capita GDP of R$66 872.84, and is served by 471 PHC units.^29 31^ A total of 35 BHUs/FHUs will be involved in the study: 34 located in São Carlos/SP and one in São Paulo/SP (Jardim Cliper), in the southern region of the city.

### Participants and outcomes

This study will include two main groups of participants: (1) individuals with one or more NCDs who receive care from PHC services and (2) healthcare professionals working in these settings who provide care to such individuals. The eligibility criteria for each group, as they relate to MARES-1, MARES-2 and MARES-3 are detailed in table 1. The primary outcome for each objective, along with the instruments and measures used for their assessment, is presented in table 2.

**Table 1 T1:** Eligibility criteria

Inclusion criteria	Exclusion criteria
MARES-1 and MARES-2	
Individuals	
Attending PHC services Diagnosed with one or more NCDs Aged ≥30 years	Clinically unstable in the past month (worsening symptoms requiring emergency care or hospitalisation) Currently pregnant Active pulmonary tuberculosis or undergoing treatment for pulmonary tuberculosis Acute respiratory infection Cognitive impairment that prevents understanding of the COLA-6 questionnaire, that is, MMSE score ≤20^48^ Contraindications to spirometry or inability to perform the test Declining to participate in the study

MARES-2	
Healthcare professional	
Providing care to individuals with NCDs attending PHC services Includes physicians, nurses, physiotherapists and community agents	Did not complete training to apply the COLA-6 questionnaire Declining to participate in the study

MARES-3	
Individuals	
The inclusion and exclusion criteria will be the same as those for individuals of MARES-1 and MARES-2, considering that this is a follow-up from these previous studies.	
Participants will be included in the follow-up phase if they meet either of the following criteria: Identified as having abnormal spirometry or diagnosis of CRD in MARES-1 Identified as being at high risk for CRD through the COLA-6 questionnaire in MARES-2	Participants will be excluded from the follow-up phase if: Clinically unstable in the past month (worsening symptoms requiring emergency care or hospitalisation) Currently pregnant Diagnosed with active pulmonary tuberculosis or undergoing treatment for pulmonary tuberculosis Presenting with an acute respiratory infection Having contraindications to spirometry or inability to perform the test Declining to participate in the study

COLA-6, short version of COPD in Low-Income and Middle-Income Countries Assessment; COPD, chronic obstructive pulmonary disease; CRD, chronic respiratory disease; FeNO, fractional exhaled nitric oxide; MARES, Multimorbidity Approach for REspiratory Solutions; MMSE, Mini–Mental State Examination; NCDs, non-communicable diseases; PHC, primary healthcare.

**Table 2 T2:** Relationship between objectives, outcomes and measures

Objectives	Outcomes	Measures
MARES-1		
To evaluate the discriminative accuracy of the COLA-6 questionnaire in identifying individuals at risk for CRDs who attend PHC services for the treatment of NCDs	Discriminative accuracy of the COLA-6 questionnaire: Area under the receiver operating characteristics curve Sensitivity and specificity of the COLA-6 questionnaire with and without PEF	COLA-6 questionnaire Spirometry
	Correlation between COLA-6 questionnaire and SBQ questionnaire	COLA-6 questionnaire SBQ questionnaire

MARES-2		
To assess the feasibility of implementing the COLA-6 questionnaire in PHC settings for NCDs care in Brazil by primary care professionals	The barriers and facilitators to implementing the COLA-6 questionnaire	Semistructured interviews with health professionals

MARES-3		
To investigate whether individuals with NCDs, who use PHC services, identified as having abnormal spirometry or diagnosis of CRD or as being at high risk for CRDs, are able to access further diagnostic and treatment services	The barriers and facilitators to accessing the healthcare system for diagnosis and treatment	Semistructured interviews with patients
Mean change in inflammation of the airways		FeNO measurement
Mean change in lung function		Spirometry
Mean change in health status		CAAT questionnaire
Mean change in asthma control		ACQ-7 questionnaire

ACQ-7, Asthma Control Questionnaire; CAAT, Chronic Airways Assessment Test; COLA-6, short version of COPD in Low-income and Middle-income Countries Assessment; COPD, chronic obstructive pulmonary disease; CRDs, chronic respiratory diseases; FeNO, fractional exhaled nitric oxide; MARES, Multimorbidity Approach for REspiratory Solutions; NCDs, non-communicable diseases; PEF, peak expiratory flow; PHC, primary healthcare; PRISm, Preserved Ratio Impaired Spirometry; SBQ, Symptom-Based Questionnaire.

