### Recruitment

For MARES-1, individuals will be recruited from PHC services, including BHUs and FHUs, located in the municipalities of São Carlos and São Paulo, Brazil. Eligible individuals with NCDs will be recruited through three primary strategies: (1) individuals receiving routine care for established NCDs at BHUs/FHUs, such as scheduled consultations for hypertension or diabetes; (2) individuals with NCDs identified through proactive outreach by community health agents and (3) individuals from BHUs/FHUs with NCDs who become aware of the study via passive recruitment strategies, including informational posters, communication from healthcare staff, peer referrals or invitations extended during service delivery days. Recruitment materials, including posters with contact details for the research team, will be displayed in BHUs/FHUs, and direct invitations will be issued during routine service encounters. All recruitment procedures will be conducted in accordance with ethical principles, ensuring the protection of participants’ rights to privacy and autonomy.

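### Table 1 admits patients whose only NCD is known asthma or COPD, against the MARES-1 objective, and the described analysis does not separate known from newly found disease

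*Protocol article*

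**What the plan says.** **Eligibility (Participants and outcomes, Table 1).** For patients in MARES-1 and MARES-2 the inclusion criteria read "Attending PHC services Diagnosed with one or more NCDs Aged ≥30 years"; the criterion at issue is "Diagnosed with one or more NCDs". The exclusions that concern the lungs are "Active pulmonary tuberculosis or undergoing treatment for pulmonary tuberculosis Acute respiratory infection" and contraindication to, or inability to perform, spirometry. A previous diagnosis of asthma, COPD or another CRD is not mentioned.

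**What counts as an NCD (Introduction).** "Chronic respiratory diseases (CRDs) are among the most prevalent chronic non-communicable diseases (NCDs) worldwide".

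**Whom the study is about.** The MARES-1 objective is accuracy in "identifying Brazilian individuals with CRDs who attend PHC services for the management of other NCDs", and the Study design overview repeats the restriction to other NCDs. The Introduction gives the reason for the work as "identifying people living with undiagnosed CRDs during routine care for other NCDs in PHC services". Table 2 restates the MARES-1 objective without the word other.

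**Recruitment.** One route is "individuals receiving routine care for established NCDs at BHUs/FHUs, such as scheduled consultations for hypertension or diabetes". The conditions named are examples. The other routes are outreach by community health agents and passive recruitment such as posters and peer referral.

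**Analysis (Data analysis, MARES-1).** AUC is calculated for combined CRDs and for each condition. Sensitivity, specificity and predictive values are calculated at a score of 4 or more, and a further cut-off is chosen to reach at least 90% sensitivity. No split by previous CRD diagnosis is described. The MARES-1 initial assessment does record medical history and current medications.

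**The concern.** Read together, Table 1 and the Introduction make a patient with diagnosed asthma or COPD and no other long-term condition eligible. That patient is outside the stated objective and is not someone a case-finding tool needs to find.

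COLA-6 scores respiratory symptoms, functional status, exposures, age and peak flow. If people with known disease score differently from people whose disease is found for the first time, pooled accuracy depends on how many known cases happen to enrol. The same applies to the cut-off chosen for 90% sensitivity, which could reach 90% in the mixture and miss it in undiagnosed patients.

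MARES-3 inherits the problem. It asks how identified people reach diagnosis and treatment, and it reports 6-month changes for MARES-1 participants. People already in respiratory care would be averaged with people who have just learned of their condition.

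**Working it through.** **1. The plan's own counts (Sample size).** 0.17 × 859 = 146 COPD cases; 146 + 77 + 86 = 309 with abnormal spirometry; 859 − 309 = 550 normal. These agree with the text. They come from overall prevalence, so known and unknown cases are counted together. The article gives no figure for the share already diagnosed.

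**2. Does the text admit known CRD?**
- Table 1: any NCD suffices, and known CRD is not excluded.
- Introduction: a CRD is an NCD.
- Hence a CRD alone satisfies Table 1.
- Objective and Study design overview: the care must be for other NCDs.

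The last line contradicts the one before it. The Recruitment section does not settle the matter, because hypertension and diabetes are only examples.

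**3. Illustration for sensitivity.** Let k be the share of COPD cases already known. Assume sensitivity of 45.7% in undiagnosed COPD and 75–85% in known COPD. The 45.7% is in the Sample size section as the earlier study's figure for COPD; assigning it to undiagnosed cases is an assumption, and so are k and the 75–85%.

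Pooled sensitivity = (1 − k) × 0.457 + k × (sensitivity in known cases)

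| k | known 75% | known 85% | shift from 45.7% |
|---|---|---|---|
| 20% | 0.3656 + 0.1500 = 51.6% | 0.3656 + 0.1700 = 53.6% | 5.9 to 7.9 points |
| 30% | 0.3199 + 0.2250 = 54.5% | 0.3199 + 0.2550 = 57.5% | 8.8 to 11.8 points |

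Unrounded, the second row is 54.49% and 57.49%, so about 54–57%. A wider set of assumptions (known share 10–50%, known-case sensitivity 60–80%) gives shifts of 1.4 to 17.2 points. For scale, the 95% half-width of a sensitivity of 45.7% in 146 cases is 1.96 × √(0.457 × 0.543 / 146) = 8.1 points.

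**4. Bound for the 90% threshold.** Suppose pooled sensitivity is exactly 90% and every known case is positive at that cut-off. Sensitivity in undiagnosed cases is then (0.90 − k)/(1 − k): 0.70/0.80 = 87.5% at k = 20% and 0.60/0.70 = 85.7% at k = 30%. This is the largest shortfall at those shares.

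**5. Precision in the undiagnosed subset.** The article states no AUC value. An equal-variance binormal curve through 45.7% sensitivity and 86.5% specificity has AUC 0.759. With 713 non-cases (859 − 146), 1.96 times the Hanley–McNeil standard error gives:

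| COPD already known | undiagnosed COPD cases | AUC half-width (points) |
|---|---|---|
| 0% | 146 | 4.8 |
| 10% | 131 | 5.0 |
| 20% | 117 | 5.3 |
| 30% | 102 | 5.6 |
| 50% | 73 | 6.6 |

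The 4.8 in the first row is not offered as a check on the article's 4.5%, whose formula and assumed AUC are not given.

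**The case against.** The strongest reply is that the MARES-1 objective never says undiagnosed. That word belongs to the rationale in the Introduction, and case numbers are planned from overall prevalence. For all attenders with an NCD the pooled estimates are valid, so the question is applicability. This stands. It means the documents do not support the inference that known CRD must be excluded or that the all-participant estimate is wrong.

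It can also be said that the objective already limits the population to other NCDs, so Table 1 is merely loose. That is a fair reading of intent, but enrolment follows the criteria, and Table 2 drops the same word. An analysis plan that is not shown may define a split by previous diagnosis; it could not correct an enrolment criterion.

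A reader might further infer that specificity will fall because treated asthma that tests normal on the day is classed as normal. The documents do not establish this. Classification follows Figure 2, which is not shown, the case group includes a diagnosis of CRD as well as abnormal spirometry, and FeNO is also used. Nor do they show that known cases score higher, since treatment could lower their scores, or that posters and referral attract respiratory patients in particular.

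Finally, Table 2 lists only barriers and facilitators for MARES-2, so there is no accuracy estimate in that part to distort.

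**Conclusion.** The point holds as an internal contradiction with a consequence for interpretation. Table 1, read with the Introduction, admits patients whom the objective leaves out, and the described analysis pools them with the patients for whom COLA-6 is intended. AUC, sensitivity, predictive values and the 90% threshold may therefore not describe case-finding performance, and MARES-3 results would mix two groups with different access to care.

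Neither the size nor the net direction can be fixed from the article. The 52–54% and 54–57% figures illustrate what the mixture could do if known cases are more often positive, with every input except 45.7% assumed and 45.7% itself assigned by assumption to undiagnosed cases. At a 20% known share that shift is smaller than the sampling half-width for sensitivity. Unlike sampling error, it would not shrink with a larger sample or show in the confidence interval.

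**What to change.** 1. **Table 1, MARES-1 and MARES-2.** Reconcile the criterion with the objective by requiring at least one NCD other than a CRD, and align Table 2. Patients with a known CRD plus, say, hypertension may stay eligible.
2. **MARES-1 analysis.** Using the medical history and medication data already collected, define previous CRD diagnosis before the data are examined. Pre-specify AUC, sensitivity, specificity, predictive values and the 90%-sensitivity threshold in participants without such a diagnosis, alongside the all-participant estimate, and show known CRD separately.
3. **MARES-3.** Report access results and 6-month changes by newly identified versus previously known CRD. The baseline history is described under a MARES-1 label, so confirm that previous diagnosis is also recorded for the MARES-2 participants who enter MARES-3.

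**Cost.** A short wording change and one subset definition, with no new measurement in MARES-1. Intervals in the undiagnosed subset will be wider, for example 5.0 to 6.6 points for the COPD AUC instead of 4.8 under the assumptions above. That should be stated rather than met by enrolling more: keeping 146 undiagnosed COPD cases would take about 939 to 1572 participants without known COPD at known shares of 10–50%, and the existing rule for extending recruitment is tied to low prevalence, not to previous diagnosis.
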